## Abstract

Multiple adjustment difficulties have been associated with children’s exposure to recent parental wartime military deployments, but long-term consequences have not yet been systematically studied. This investigation will assess direct and indirect relationships between exposures to parental deployments early in life and later youth adjustment. Parents’ psychological health and family processes will be examined as mediators, and parents’ and children’s vulnerability and support will be examined as moderators. Archival data will be combined with new data gathered from two children and up to two parents in families where children will be aged 11 to 16 at the first data collection and will have experienced at least one parental deployment, for at least one child prior to age 6. Data are being gathered via telephone interviews and web-based surveys conducted twice one year apart. Outcomes are indicators of children’s social-emotional development, behavior, and academic performance. Notable features of this study include oversampling of female service members, inclusion of siblings, and inclusion of families of both veterans and currently serving members. This study has potentially important implications for schools, community organizations and health care providers serving current and future cohorts of military and veteran families.

## Introduction

Multiple short-term adjustment difficulties, including elevated behavior problems [1, 2], risk-taking and suicidal thoughts [3],impairments in academic performance, and difficulties with peers [4] have been associated with recent exposure to parental wartime deployment among the approximately two million children of U.S. military personnel who have served in ongoing conflicts in Iraq, Afghanistan, or other combat zones since 2001 [5] Exposures to parental wartime deployments may have long-term consequences for children, particularly when exposures occur early in life [6, 7], but these have not yet been systematically studied. These early adverse experiences could challenge the foundation for children’s later emotion regulation and relationship functioning [8, 9]. The consequences of early exposures to adversity may be particularly evident during adolescence [10, 11] when young people make decisions about substance use, risky behavior, and peer relationships that are highly consequential for their later functioning [9]. Evidence suggests that substantial percentages of these youth are troubled–in 2013, for example, military children in California in 9th or 11th grades were 43% more likely than civilian peers to have considered suicide [12]. There is considerable variability, however, in children’s responses to parental deployments, highlighting a critical knowledge gap in understanding explanatory factors associated with both negative and positive adaptation [10, 13].

### Model for the proposed study

Theory and limited existing evidence suggest that exposure to parental deployments early in life is directly related to children’s later outcomes (see Aim 1 in Fig 1) [6, 14].Separation from a parent is well-established as a consequential adverse experience for children, with implications for later psychological [15, 16] and behavior problems [15]. In one study, sleep disturbances in adulthood were linked to separations lasting only one month during the first year of life [17]. Wartime separation from a military parent may be especially distressing, as children experience worry and fear about the deployed parent as well as concern about their at-home parent [18]. One of the preliminary studies for this research was the first to examine the implications of exposure timing in the lives of young children, finding for example that prenatal exposure to parental deployment was significantly related to peer problems among 6 to 10 year olds [19]. These direct relationships may differ, however, across siblings in the same family due to personal characteristics or differences in the timing of exposure. This study will be the first to address this issue.

**Fig 1 pone.0295007.g001:**
[figure not shown]
Conceptual model.

The mediated relationships between exposure to parental deployment and youth outcomes in the model for this study are guided by research about risk and resilience in families. Four possible mechanisms will be tested in this study (see Aim 2 in Fig 1). For both returning service members and at-home partners, parents’ psychological health (i.e., during- or post-deployment depression, anxiety, PTSD, or substance use) is associated with multiple adjustment difficulties in children [20–22] and similar relationships are expected here. Other indirect pathways travel through family relationships, which have been studied less in relation to deployment than other mechanisms. Here, guided by findings that ‘risky’ families [23, 24] and resilience in families [25, 26] have substantial effects on children’s long-term outcomes, youth outcomes are expected to be worse when deployment is associated with parenting behavior that is hostile or emotionally cold rather than warm and responsive [23, 24], and better when the reverse is true. Existing research indicates that parents in military families report more difficulties, and in some cases compromised caregiving quality, during and following deployment [5, 27, 28].

With regard to marital or partner relationships, the Institute of Medicine [5] concluded the evidence is ‘strong’ that service members returning from combat deployments are at elevated risk of marital conflict and violence [92
93]. Research in the general population indicates that interparental conflict can disrupt children’s long-term outcomes, resulting in elevated emotional insecurity and internalizing and externalizing problems [29]. Although research with military families on this topic is rare, one recent study found that, during reintegration, interparental conflict was negatively related to youth’s self-efficacy and well-being and positively associated with their anxiety and depressive symptoms [30]. More positive youth outcomes are thus expected when there is less conflict, more constructive communication, and better cooperation between parents.

With regard to family functioning, family resilience theory suggests that resilience is more likely to occur in the aftermath of adversity when multiple family members perceive that their family is cohesive, well-organized, able to communicate and solve problems effectively, and shares a sense of optimism and confidence that life has meaning [26, 31]. Importantly, this study will advance research on military families by assessing sibling relationships as a critical family relationship context. Past research with civilian families has found that positive family interaction mediates relationships between risk factors (e.g. parental depressed mood, marital conflict, cumulative risk) and children’s adjustment [32, 33]. Studies of civilian populations highlight how siblings’ relationships with one another constitute unique risk and resilience factors for youth adjustment [34]. In this study, more positive youth adjustment is expected when multiple family members—with specific attention to siblings–report and demonstrate that the family is functioning well [29].

To date, most evidence about moderating relationships involving deployments and children’s outcomes (see Aim 3 in Fig 1) has focused on characteristics of individual children (e.g., age) or service members (e.g., active vs. reserve), with mixed results [6]. Deployments do not occur in isolation, however. The Army STARRS [35], Millennium Cohort [36], and other studies [37] suggest that prior exposure to adversity moderates service members’ later vulnerability to traumatic deployment experiences. As a result, the sample for this study was intentionally selected based on military parents’ exposures to adverse experiences prior to deployment. Similarly, children’s exposure to parental deployment may be an isolated experience, or it may join—or launch—a ‘caravan’ of other adverse experiences shaping later adjustment, helping to explain diversity in children’s outcomes [38]. Parents’ and children’s lifetime exposures to adversity and perceptions of support will be treated as potential moderators of relationships between deployment and intervening or outcome variables. Comparing two siblings in each family will allow separation of child-specific factors from those of deployment or parental factors in relation to children’s outcomes, a significant contribution to the risk and resilience literature.

This study also is designed to permit consideration of both parent and youth sex as moderators of the relationships between early exposure to parental deployments and later youth adjustment. There are good reasons to expect that mothers’ deployments may be especially impactful or that boys and girls may be differentially vulnerable, but existing evidence is mixed.

Consistent with Masten and Narayan’s [39] recognition that the developmental timing of adverse experiences is consequential, deployments, life events, and other experiences will be coded in ‘child time’ (i.e., months since birth), including exposures occurring prenatally, as well as timing relative to deployment. More positive outcomes are expected when exposures began later and were less frequent or prolonged, and/or when parents experienced fewer traumatic experiences during deployment. The controlled heterogeneity of deployment timing in this study will help to provide greater clarity about the role of child age in these effects, thus addressing the lack of consistency in previous findings in relation to deployment effects.

### Aim 1: To assess direct relationships between the timing, frequency, duration and nature of siblings’ early exposures to parental deployments and later youth adjustment

Youth whose deployment exposures began earlier in childhood, were more frequent or prolonged, and/or involved more traumatic [40] parental experiences are hypothesized to display less positive adjustment, and youth exposed to deployments with fewer such characteristics will display more positive adjustment. We will examine how these direct relationships differ between siblings, providing more sensitive tests than previously possible of the degree to which youth outcomes are a function of deployment, family, and child factors.

### Aim 2: To assess the role of parents’ psychological health and family processes in mediating relationships between siblings’ early exposures to parental deployment and later youth adjustment

Mediation is hypothesized to occur through four pathways: a) parents’ psychological health; b) parenting efficacy; c) the quality of parents’ relationship with one another; and d) the quality of family functioning, with particular attention to the quality of sibling relationships, each of which is expected to be positively related to youth adjustment.

### Aim 3: To assess the moderating role of parent and sibling sex, and vulnerability and support in the relationship between siblings’ early exposures to parental deployment and later youth adjustment

Relationships between parental deployments and youth adjustment are expected to be stronger in the presence of greater vulnerability (i.e., adverse experiences, mental health problems) and less support (i.e., availability and use of formal and informal support) prior to and following deployment. Parent and youth sex will be examined as potential moderators of the impact of the relationship between exposure to parental wartime deployment and outcomes.

Existing studies of military children are limited by significant design constraints, such as focusing only on current or recent deployments, which leaves unanswered questions about long-term consequences [10]. Few studies have included data about military parents’ experiences before deployment, which may lead researchers to attribute to deployments parental factors that not only existed before, but may have conditioned parents’ reactions to deployment. Most studies have relied almost completely on parents’ reports for data about children, which can be influenced by parents’ own symptoms [41]. Few studies have compared the consequences of mothers’ and fathers’ deployments, none in the long term. The proposed study is unique because its combination of archival and new data surmounts these design constraints of existing studies.

## Methods

### Overview of study design

This study will combine archival data with new data gathered on two occasions 12 months apart. Data are being gathered via telephone interviews and supervised self-administered surveys with two siblings and up to two parents in 712 families.

This study is being conducted with oversight by the Institutional Review Board at the Naval Health Research Center (Protocol Number: NHRC.2019.0019). The Institutional Review Board at Purdue University approved deferral to the Naval Health Research Center IRB (Purdue IRB-2020-440) and the Army Human Research Protections Office concurred with the determination made by the Naval Health Research Center IRB (HRPO; Log Number: E02093). The study also was reviewed by the Department of Defense Office of People Analytics and issued DoD Survey License Exemption (#9)—Exempt#-0100. The Office of Military Family Readiness Policy in the U.S. Department of Defense is serving as the DoD sponsor of data requests. Parents provide written consent for their own and their children’s participation; adolescents provide written assent for their own participation.

Archival data will include demographic, deployment, and medical records from DOD sources. Demographic variables will come from the Defense Enrollment Eligibility Reporting System (DEERS), and will include military career information such as service branch and component, dates of accession and promotion; personal variables such as birthdate, gender, race/ethnicity; and family information such as spouses’ and children’s names, genders, and birthdates; and family contact information.

Deployment history information will come from the Contingency Tracking (CTS) and Personnel Tempo (PERSTEMPO) files, and will include reasons for deployment (e.g., training, contingency operations), dates, locations, and hazardous duty pay status. Medical record data will include health care utilization and diagnoses from the Medical Data Repository (MDR) including mental health diagnoses of both parents since the first deployment of the service member(s); parents’ physical injuries resulting from operations of war and screening and diagnosis of Traumatic Brain Injury; and children’s lifetime outpatient and inpatient visits with documentation of childhood disorders (e.g., Autism) and psychiatric disorders (e.g., mood and anxiety disorders). Outcomes of interest will include multiple indicators of children’s social-emotional development, behavior, academic performance, and health. Analyses will focus on multilevel examinations of direct, mediated, and moderating relationships between early exposure to parental wartime deployment and later youth outcomes. The study has been approved by the Institutional Review Board at the Department of Defense Naval Health Research Center. Data collection began in the spring of 2023, and recruitment is expected to continue for 16 months.

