**Mediating Processes**			
**1. Parents’ Mental Health.**			
***a. Psychological health*:**	Anxiety (GAD-7) (α = .92); [61]	Survey	
	Depression (PHQ-8) (α = .85); [62, 63]	Survey	
	Post-traumatic stress PCL-5 (α = .94); [64, 65]	Interview	
	Spirituality DURAL (α = .78 to .91) [66]	Interview	Interview
	General Life Satisfaction [59]	Survey	
	Meaning and purpose (α>.90) [59]	Survey	
***b. Alcohol use*:**	AUDIT (α = .80); [67, 68]	Survey	
***c. Post-traumatic growth*:**	Post-traumatic Growth Inventory Short Form (10; α = .89);[69]	Survey	
***d. Medical records*:**	MDR records psychiatric diagnoses since deployment: • Mood Disorders (296.0–296.9, • Anxiety Disorders (300.0–300.9), and • Psychoactive Substance Use; 303.0–305.8.	Records	

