**Moderating Relationships**			
**1. Parents’ Vulnerability Prior to Deployment.**			
***a. Life History***	Family members arriving or leaving; moving; changing schools, Parents: Adverse Childhood Experiences (ACES)	Interview	Interview
***b. Adverse Childhood Experiences***	Parents: Adverse Childhood Experiences (ACES)	Interview	
***c. Family of Origin Functioning***	Subscale of Deployment Risk & Resilience Inventory (α = .85); [83]	Interview	
***d. Psychological symptoms or substance use*:**	*MDR* records for psychiatric diagnoses including Mood Disorders (296.0–296.9, Anxiety Disorders (300.0–300.9), Psychoactive substance; 303.0–305.8;	Records	

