### Innovation

The proposed research is unique in its purpose, and its approach improves in multiple ways on existing studies of military children. It is the first to systematically examine the long-term impact of parental deployment with explicit attention to the timing of children’s exposure. It is the first nationally representative study to incorporate multiple offspring per family (i.e., siblings), allowing examination of child-specific effects while controlling for deployment and parent factors [126, 127]. It is designed to include a sufficient number of female service members to permit comparison of mothers’ and fathers’ deployments, and it takes steps to avoid bias toward ‘healthy warriors’ (a bias that can occur in studies of military members because personnel who have been injured tend to leave military service, leaving behind an increasingly distilled population of ‘healthy warriors’), such as including families who have completed their service and stratifying based on early exposure to adversity. It uses archival data and parents’ reports to identify adverse experiences and vulnerabilities in place prior to deployment [128]. Archival records also will provide precise information about frequency, duration, timing, and location of deployments, as well as objective information about medical visits and diagnoses for all participants. Unlike most research on military families, it explicitly attends to both positive and negative outcomes for children, not just in relation to parental deployments, but also in relation to caravans of support or adversity that may accompany them. Multiple equation modeling will allow estimation of variability both within and between families over time, account for dependencies of within-family data, and measurement error and missing values inherent in surveys, and correct for unequal probabilities of sample selection [86, 129, 130].

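### The stated start of the parents' medical record window conflicts with the pre-deployment psychiatric moderator that Table 2 takes from those records

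*Protocol article*

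**What the plan says.** Under Overview of study design, the protocol article describes the MDR data. For parents it names "mental health diagnoses of both parents since the first deployment of the service member(s". For children, in the same sentence, it names "children’s lifetime outpatient and inpatient visits".

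The section Administrative data and measures describes the MDR request again, for every child and parent, without a start date.

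Table 2 uses parents' MDR psychiatric diagnoses twice:

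- As a mediator, under Parents' Mental Health, item d: "MDR records psychiatric diagnoses since deployment".
- As a moderator, under "Parents’ Vulnerability Prior to Deployment", item d, which covers psychological symptoms or substance use. Records are the only source listed.

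The Aim 3 statement expects stronger relationships with "greater vulnerability (i.e., adverse experiences, mental health problems) and less support", and places these "prior to and following deployment". The Innovation section claims: "It uses archival data and parents’ reports to identify adverse experiences and vulnerabilities in place prior to deployment".

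**The concern.** A record extract that opens at the first deployment holds no diagnosis made before it. Yet the article needs such diagnoses for one Aim 3 moderator and presents archival evidence from before deployment as a strength of the study.

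The risk lies in how the gap might be filled. The Aim 3 analysis expects the path from deployment to the mediators to be steeper in more vulnerable parents, and parents' psychological health is one of those mediators. If later diagnoses were used as the vulnerability measure, the analysis would condition on a possible consequence of deployment, and one variable would serve as both moderator and mediator indicator. The Aim 3 section itself criticizes earlier work for attributing to deployment parental factors that were already there. For psychiatric history, the stated window would leave this study open to the same criticism.

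**Working it through.** The article gives no figure for this point, so the check compares sources, codes and windows.

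| | Overview (archival data) | Table 2 mediator, item d | Table 2 moderator, item d |
|---|---|---|---|
| Source | MDR | MDR | MDR |
| Codes | mental health diagnoses, no codes given | 296.0–296.9, 300.0–300.9, 303.0–305.8 | 296.0–296.9, 300.0–300.9, 303.0–305.8 |
| Window | from first deployment | from deployment | before deployment |

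1. *Is the overview limit deliberate?* It reads that way. The same sentence gives children a lifetime window and parents a later start, so windows were chosen person by person. No other place in the article gives a start point for the parents' records.

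2. *Reading A: the overview describes the whole extract, and the dividing deployment is the service member's first.* The extract and the moderator's period do not overlap, so the moderator item is empty. The parents concerned number 712 × 1.66 = 1,181.92, which the article gives as 1,182. If the item were filled from this extract anyway, all three rows of the moderator column would match the mediator column.

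3. *Reading A with a different anchor.* Eligibility (Sample section) rests on a wartime deployment of at least 90 days shared by both siblings. It is not said to be the service member's first. Where it came later, the extract holds records between the first deployment and the shared one. That gives a partial measure before the qualifying deployment, but one taken after an earlier deployment. The article does not say which deployment divides before from after.

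4. *Reading B: the extract has no start limit,* as the section on administrative data allows. Diagnoses can then be sorted by date, the two Table 2 rows separate cleanly, and only the overview wording is wrong.

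5. *Does another measure stand in for the item?* The other three of the four items under the same moderator heading (life history, adverse childhood experiences, family-of-origin functioning) come from interviews. They carry adversity before deployment, but none is clearly a record of the parent's own earlier psychiatric diagnoses.

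6. *How far does it reach?* One item of four in one moderator domain. On the mediator side, MDR diagnoses are one indicator among several; the others are scales answered by the parents, such as those for anxiety, depression, post-traumatic stress and alcohol use.

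**The case against.** The best defense is that the overview sentence is a summary, not the data specification. It is open-ended: "Medical record data will include health care utilization and diagnoses from the Medical Data Repository (MDR) including mental health diagnoses of both parents". It may mention only the use of MDR data that serves the mediator. The more specific places point the other way: the request has no start date, Table 2 assigns MDR records to the period before deployment, and the Innovation section does likewise. Table 2 also labels the two periods separately, and the article plans to code experiences by their timing relative to deployment, so shared codes are what one expects when one construct is measured in two periods. Finally, this is a journal article, and the actual data request is not shown.

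Much of this stands. A reader might infer that the moderator cannot be built, that it will coincide with the mediator, or that none of the parents' time before deployment is covered. The documents do not support these as facts. Each holds only under the narrow reading of the overview, and the last also assumes that the first deployment is the anchor. Nor does the article say that later diagnoses would fill the moderator.

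What the defense does not remove is the contradiction. The date limit is attached to exactly the item that the moderator needs, and a description that omits a date does not cancel one that states it. An analysis plan cannot repair this either if the records are never requested.

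**Conclusion.** The article contradicts itself on the window of a data source on which one Aim 3 moderator component wholly depends. If the overview is followed as written, that component has no diagnoses from before the first deployment. If the real request reaches further back, a correction of wording is enough. The documents do not settle which applies.

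The effect is limited to the diagnosis component of parents' vulnerability before deployment. Adversity, including the screening used for the risk strata, does not depend on these records. The interview-based vulnerability measures, social support, and parent and youth sex as moderators also stand. The advantage claimed over earlier studies is weakened for psychiatric history, not lost. The point is worth settling because the article still speaks of the administrative data as to be requested, so the window can apparently still be set.

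**What to change.** Reconcile the overview, the section on administrative data, both Table 2 rows and the Innovation claim:

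- Have the parental MDR window begin before the first deployment: from accession for the service member, or from the start of available coverage.
- Name the anchor deployment, either the service member's first or the one shared by both siblings, and use it throughout.
- Split diagnoses at the start date of that deployment. Earlier ones form the Aim 3 moderator and later ones the Aim 2 mediator, with no overlap.
- If earlier records cannot be obtained, remove MDR diagnoses from the pre-deployment moderator and narrow the Innovation claim to what the interviews supply.

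The cost is small: the same data source and the same persons over a longer period, with possibly a minor data-request or IRB amendment. If the request already reaches back far enough, only the text changes.
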